Considering the settings presented, we believe that motor and cognitive ability acquired through VR games might facilitate computer utilization, which is a valuable communication tool.^[17]^ Therefore, we intend to assess, through a loneliness scale, a group of older adults that are initiating computer classes for beginners. The effects of practicing games using VR within computer classes will be compared to the impact of conventional computer classes. Games with VR, requiring a variety of different motor and cognitive abilities will be used to identify whether evolution in loneliness, is related to the practice of tasks using virtual ICTs. We hypothesized that the practice of VR games added to conventional computer classes will lead to an improvement in motor ability and less loneliness of older adults.

Thus, the main objective is to evaluate the effects of practicing games in a VR environment during computer classes on loneliness among students of an elderly reference center (ERC). Moreover, in students initiating computer classes for seniors, we aim to: evaluate the evolution in time of response during the practice of VR games; evaluate the evolution in performance of practice of VR games; and evaluate the relation between motor ability to loneliness.

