### Study population

2.1

It will be a convenience sample. The participants will be students in beginning level computer classes for seniors in the CRI in Ribeirão Pires, Sao Paulo, Brazil.

Because no study was found using the short version of the Social and Emotional Loneliness Scale for Adults (SELSA-S) before and after any intervention, sample calculation was not possible. However, there will be a minimum of 23 participants in this study, based on the largest sample that used VR in older adults found in the literature.^[13]^

The CRI Ribeirão Pires offers cultural, sportive, and intellectual activities for people over 50 years old, as used in the multicenter Studies on Global Ageing and Adult Health project of the WHO.^[19]^

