### Primary outcomes

8.1

Data on loneliness will be collected by administering the SELSA-S and evaluated as a total and also divided in 3 subscales: romantic, social, and familiar. Higher scores indicate a higher level of loneliness, while lower scores indicate a lower level of loneliness.

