### Data analysis

8.3

Excel and SPSS version 2.1 for Windows will be used for data preparation and analysis. The significance level will be *P* ≤ 0.05.

The data will be presented as means and standard deviations and in frequency tables. Before the data analysis, the normality of all variables will be evaluated for skewness and kurtosis. To compare participants’ mood and loneliness, paired *t* tests, Kruskal–Wallis tests, Mann–Whitney *U* tests, or Pearson correlation coefficients will be used. The analysis will be blinded and will compare the 3 moments of data collection and the 2 groups (G1 and G2). To guard against the possibility of type 1 errors from making too many post hoc comparisons, we will carry out only those comparisons that have been planned based on our hypotheses.

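### The SELSA-S total and its three subscales are listed as primary without ranking and each judged at 0.05; limiting the analysis to planned comparisons does not control the error across them

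*Protocol article*

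**What the plan says.** Under Primary outcomes (8.1), loneliness is measured by the SELSA-S and "evaluated as a total and also divided in 3 subscales: romantic, social, and familiar". That makes four scores under the primary heading, with no order among them.

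Under Data analysis (8.3), one level covers everything: "The significance level will be *P* ≤ 0.05". The analysis "will compare the 3 moments of data collection and the 2 groups (G1 and G2"), and the candidate methods are given as a list of alternatives: "To compare participants’ mood and loneliness, paired *t* tests, Kruskal–Wallis tests, Mann–Whitney *U* tests, or Pearson correlation coefficients will be used". No method is tied to a particular score or contrast. The section closes with the only statement on type I error: to guard against errors from too many post hoc comparisons, "we will carry out only those comparisons that have been planned based on our hypotheses".

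The hypothesis that would define what is planned is in the Introduction. It says that VR games added to conventional classes "will lead to an improvement in motor ability and less loneliness of older adults". It names no SELSA-S score, time point or contrast.

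**The concern.** Deciding comparisons in advance stops the data from suggesting further tests. It does not change the arithmetic of making several tests at 0.05 each. The hypothesis speaks of loneliness in general, so it rules out none of the four scores, and the restriction to planned comparisons leaves all four in place.

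At stake is what counts as a positive trial. The Discussion says the study will settle whether VR games reduce loneliness. Under the text as written, a significant difference on one subscale alone, with nothing on the total, could be presented as a primary finding. The sample gives no counterweight: the Study population section says "sample calculation was not possible" and sets a minimum of 23 participants, so no primary score was singled out through a power calculation either.

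**Working it through.** The article gives no family-wise error rate, so there is no figure of its own to reproduce beyond the level of 0.05 for a single test.

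**Inputs from the article**
- Level per test: 0.05 (8.3)
- Scores under the primary heading: 4, the total plus 3 subscales (8.1)
- Contrast of interest: VR added to classes against conventional classes (Introduction), counted once

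**Inputs assumed**
- Two-sided tests (sidedness is not stated)
- Total equal to the unweighted sum of the three subscales
- Common correlation r between subscales of 0, 0.3, 0.5 or 0.7
- Each single test has its nominal 5% error

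**Step 1: reference values.** If four tests were independent, the chance of at least one false positive would be 1 − 0.95^4 = 0.1855. The Bonferroni bound, which holds under any dependence, is 4 × 0.05 = 0.20.

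**Step 2: why independence does not apply.** If the total is the sum of three equally variable subscales with correlation r, its correlation with each subscale is (1 + 2r)/√(3 + 6r) = √((1 + 2r)/3). That is √(1/3) = 0.58 at r = 0 and √(2.4/3) = 0.89 at r = 0.7. The total is therefore clearly correlated with its parts even when the parts are unrelated.

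**Step 3: allow for the dependence.** Under the global null, draw three standard normal statistics Z1, Z2, Z3 with correlation r. Set the total to (Z1 + Z2 + Z3)/√(3 + 6r), and count a false positive when any of the four exceeds 1.96 in absolute value. The unadjusted column uses 1,000,000 replicates; the Bonferroni column uses 500,000.

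| r | Four scores, each at 0.05 | Three subscales only, each at 0.05 | Four scores, Bonferroni at 0.05/4 = 0.0125 |
|---|---|---|---|
| 0 | 0.161 | 0.143 | 0.044 |
| 0.3 | 0.144 | 0.136 | 0.039 |
| 0.5 | 0.129 | 0.125 | 0.036 |
| 0.7 | 0.111 | 0.109 | 0.031 |

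**Reading the table.** With one contrast and four unranked scores, the error is 0.11 to 0.16, or 2.2 to 3.2 times the nominal 0.05 (0.111/0.05 and 0.161/0.05). Nearly all of the excess comes from the subscales, which is why moving them out of the primary set resolves it. One score on one contrast brings the primary error back to 0.05 by construction.

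**The case against.** **The sentence is accurate for what it targets.** It speaks of post hoc comparisons, and restricting the analysis to planned ones does address those. A reader might infer that the article claims family-wise control that it lacks. It does not: no family-wise level is stated. This objection stands, and the sentence should be kept. What remains is that it is the only type I measure in the article and it does not reach the planned primary tests.

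**Four co-primary endpoints are not declared.** The total is mentioned first, the subscales follow as an addition, and the main objective refers to loneliness as a whole. That reading is fair, but the heading is plural and nothing gives the total precedence. Someone following the text could treat any of the four as primary.

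**The error might be put much higher.** A reader might multiply four scores by three pairwise comparisons of the moments and quote 1 − 0.95^12 = 0.46. The documents do not support that figure. The planned contrasts are not listed, so twelve is a guess. Independence is impossible for a total and its parts, and for three differences among three moments; allowing for both, the same simulation approach gives 0.25 to 0.36. Moreover, G1 and G2 receive the two conditions in opposite order, so a change between moments pooled over groups does not compare VR with conventional classes. It is not a route to a positive result on the hypothesis.

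**A fuller plan might settle it.** An analysis plan that is not shown could rank the scores. The article nevertheless fixes the primary list, the level and the safeguard itself, and these do not fit together as they stand.

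**Conclusion.** The point holds in a limited form. Four unranked primary scores, each judged at 0.05 on one VR-versus-conventional contrast, give about an 11% to 16% chance of at least one false positive, and planning those tests beforehand does not reduce it. The range rests on assumed subscale correlations of 0.7 to 0, a total that is the simple sum of the subscales, two-sided tests, and single tests that keep their nominal level. The last condition needs separate care because whole classes are randomised, six in all; any error from ignoring this is not in the range. More than one primary contrast would raise the figure, but the article does not say how many there are, so no larger number is claimed here.

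**What to change.** - In Primary outcomes, name the SELSA-S total as the single primary score.
- In Data analysis, state that it is tested once, at two-sided 0.05, on one contrast of VR against conventional classes that uses both cross-over periods and respects randomisation by class. A comparison of G2 with G1 at T1 alone would also be a single test, but it would leave phase 2 out of the primary analysis.
- Make the romantic, social and familiar subscales secondary, as well as the remaining moment and group contrasts. Either apply Holm across the three subscales or report estimates with confidence intervals and no claim of significance.
- Keep the planned-comparisons sentence and add that it limits post hoc testing and does not replace the control above.

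The primary claim then carries a 5% error, and Holm, if used, holds the subscale family at 5% separately. The ranking takes a few sentences and no extra data. Specifying the contrast takes more thought, because there are only six classes, three per group. The downside is that a significant subscale without a significant total can no longer be claimed as a primary finding.

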## Ethics and dissemination

9

This research project was approved by the Ethical Committee of the Faculdade de Medicina do ABC, Sao Paulo, Brazil, under the number 52305215.3.0000.0082.

This clinical trial register was titled “Virtual Reality Games for Elderly Socialization,” on August 17, 2016 at “ClinicalTrials.gov” (NCT02798081).

Signatures of all participants on the informed consent form will be obtained before data collection starts.

All the researchers will have access to the final trial dataset. The results will be available for the participants and their institution, and they will also be published in scientific journal, always keeping the confidentiality of the participants.

## Discussion

10

Aging is a natural process of physiological, anatomical, and emotional changes that may reduce socialization and lead to loneliness. Therefore, older adults should learn how to use communication tools in different ways, aiming to maximize social interaction.

VR offers opportunities for older adults to experience various situations in an individual and safe way.^[33]^ Virtual environments also allow people with some difficulty, when connected to or immersed in them, to improve their levels of interaction with the environment.^[34]^

This study will determine whether the practice of games in a VR environment in addition to the usual computer classes reduces loneliness among students at an ERC. Changes in loneliness, reaction time, and performance in the games, as well as the relation between motor ability and loneliness, will also be investigated.
